#### **Follow-up Period: 24 h to D4 $\pm$ 1**

During the follow-up period, the subject will complete relevant examinations and complete the safety assessment according to the study flow chart.

### **Subject Selection and Withdrawal**

Inclusion of eligible subjects is a key step to achieve the intended objectives of this clinical trial. The subjects must meet the following criteria to be allowed to participate in this study. All medical or non-medical conditions of each subject are within consideration in deciding whether he/she is eligible for the study.

#### **Inclusion Criteria**

Subjects will be eligible for enrollment into the study if all of the following criteria are met:

- 1) Before starting any trial-related activity, the subject must voluntarily sign the ICF, fully understand the purpose and significance of this trial, and willingly comply with the study procedures;
- 2) Subjects who will undergo selective abdominal surgery (laparotomy or laparoscopy) under general anesthesia for  $\geq$  1 h;
- 3) 18 to 65 years of age, male or female;
- 4)  $18.0 \text{ kg/m}^2 \leq \text{body mass index (BMI)} \leq 28.0 \text{ kg/m}^2$ ;
- 5) ASA I-II;
- 6) NRS  $\geq$  4 at rest at any time within 4 h after the surgery.

#### **Exclusion Criteria**

Subjects will be ineligible for enrollment into the study if any of the following criteria is met:

1. Disease conditions
  - 1) Have a prior history of vestibular dysfunction or have dizziness, nausea, retching or vomiting within 1 week prior to screening;
  - 2) Have a prior history of ischemic stroke or transient ischemic attack (TIA);
  - 3) Have a prior history of difficult airway, such as obstructive sleep apnea syndrome;
  - 4) Have prior reflux esophagitis;
  - 5) Have a history of myocardial infarction or unstable angina pectoris, or severe arrhythmia such as atrioventricular block grade II or higher, or NYHA functional class II or higher within 6 months prior to screening;

- 6) Have a prior history of psychiatric disorders (e.g. schizophrenia, depression, etc.), cognitive dysfunction, epilepsy, or Parkinson's syndrome;
- 7) Have advanced malignancies or malignant tumors with extensive metastases;
2. General examination/laboratory tests
  - 1) Subjects who do not receive formal antihypertensive therapy or have inadequate blood pressure control (systolic blood pressure  $\geq 160$  mmHg or  $\leq 90$  mmHg at screening, and/or diastolic blood pressure  $\geq 100$  mmHg or  $\leq 60$  mmHg at screening, excluding abnormalities from entering the operation room to postoperative extubation of endotracheal intubation);
  - 2) QTc at screening:  $> 450$  ms for males and  $> 470$  ms for females (QTc calculated by Fridericia's formula);
  - 3) Transdermal oxygen saturation ( $\text{SpO}_2$ )  $< 90\%$  at screening (excluding abnormalities from entering the operation room to postoperative extubation of endotracheal intubation);
  - 4) Poor glycemic control at screening: random blood glucose  $\geq 11.1$  mmol/L;
  - 5) Abnormal liver function at screening: aspartate aminotransferase (AST) and/or alanine aminotransferase (ALT)  $\geq 1.5 \times \text{ULN}$  and/or total bilirubin (TBIL)  $\geq 1.5 \times \text{ULN}$ ;
  - 6) Abnormal renal function at screening: serum creatinine (Cr)  $\geq 1.5 \times \text{ULN}$ ;
  - 7) Coagulation abnormalities at screening: prolonged prothrombin time (PT) exceeding the upper limit of normal by 3 seconds and/or prolonged activated partial thromboplastin time (APTT) exceeding the upper limit of normal by 10 seconds;
  - 8) Have positive infectious disease screening for hepatitis B surface antigen (HBsAg), hepatitis C antibody (HCVAb), treponema pallidum antibody or human immunodeficiency virus (HIV) antibody at screening.
3. Drug use
  - 1) Known allergies to opioids and other drugs that may be used during the trial, such as nonsteroidal anti-inflammatory drugs, antiemetics, etc.;
  - 2) Consecutive use of opioid analgesics for more than 10 days for any reason within 3 months prior to randomization, or the time of last dose is less than 5 half-lives from randomization, including but not limited to the following drugs with analgesic effect: selective  $\alpha_2$ -adrenoceptor agonists, opioid agonists/antagonists, nonsteroidal anti-inflammatory drugs, sedatives, monoamine oxidase inhibitors, glucocorticoids, CYP2D6, CYP3A4 and CYP3A5 inhibitors/inducers, antihistamines, antiepileptics, anxiolytics, antidepressants, etc. Refer to the Table of Prohibited Drugs for specific drugs;
4. Others
  - 1) Have a history of drug abuse and/or alcohol abuse within 1 year prior to screening, i.e.,

more than 15 g of alcohol per day on average (15 g alcohol is equivalent to 450 mL of beer or 150 mL of wine or 50 mL of low-alcoholic liquor);

- 2) Positive drug abuse screening result at screening;
- 3) Pregnant or lactating women;
- 4) Subjects who have a birth plan, are unwilling or unable to take effective contraceptive measures from 30 days before screening to half a year after the end of the trial;
- 5) Subjects who participated in other drug clinical trials (defined as receiving investigational product or placebo) within 3 months prior to screening;
- 6) Other conditions that in the opinion of the investigator make the subject unsuitable to participate in this clinical trial.

## **Investigational Products**

### **Overview of Investigational Products**

#### **Supplies**

The investigational product (SHR8554 Injection and placebo) are prepared in a workshop that complies with GMP [Good Manufacturing Practices] and has passed the test according to the specifications approved by the National Medical Products Administration. Morphine hydrochloride injection is manufactured by Shenyang First Pharmaceutical Co., Ltd., Northeast Pharmaceutical Group.

#### **Dosage Form and Strength**

SHR8554 Injection, dosage form: injection, strength: 1 mL: 1 mg, 5 mL: 5 mg, manufactured by Jiangsu Hengrui Pharmaceuticals Co., Ltd. Storage conditions: sealed, stored below 30 °C. Morphine hydrochloride injection, dosage form: injection, strength: 1 mL: 10 mg, manufactured by Shenyang First Pharmaceutical Co., Ltd., Northeast Pharmaceutical Group. Storage conditions: protected from light and sealed.

Placebo, dosage form: injection, strength: 5 mL, manufactured by Jiangsu Hengrui Pharmaceuticals Co., Ltd. Storage conditions: sealed, stored below 30 °C.

#### **Management, Dispensing and Return**

The investigational products in this clinical study are managed in accordance with relevant regulations. The unblinded drug management personnel shall prepare the investigational products according to the corresponding group of the subject randomization number. The clinical study institution shall sign the drug receipt form in duplicate, and the clinical study institution and the sponsor shall each keep one copy. The test facility should store all sealed drugs below 30 °C in a special double-locked cabinet kept by two persons according to the

storage requirements of the investigational products. Dispensing and return of each investigational product should be timely documented in the corresponding record sheet. During and after the study, the remaining drugs, packaging boxes and labels shall be promptly collected. The two parties shall sign the drug recovery form. All clinical investigational products shall be properly kept, and submitted to the sponsor after the study. The clinical investigational products shall not be transferred to any non-clinical trial participants or third parties. The unblinded monitor is responsible for monitoring the supply, use, storage of the study drugs and disposal of the remaining drugs.

### **Configuration of Investigational Products and Setting of PCA Pump Parameters**

Refer to relevant SOPs for configuration of investigational products and setting of PCA pump parameters.

### **Destruction**

Since SHR8554 Injection is a narcotic drug, it needs to be destroyed according to the requirements of the drug administration at each site, and the sponsor or its authorized personnel may provide guidance on the destruction of unused investigational products. If the study site is authorized to destroy the investigational products, the investigator must ensure that the destruction complies with applicable provisions such as applicable environment regulations, site policies, etc., and provide the process of destruction. All destruction should be well documented.

### **Randomization and Blinding**

Using a central randomization method, 528 subjects will be randomized in a 1:1:1:1 ratio to 4 treatment groups: SHR8554 Injection 0.75 mg, SHR8554 Injection 1.0 mg, placebo, and morphine hydrochloride injection.

The random number table will be generated by an unblinded statistician of the statistical team using SAS 9.4, and the blinding will be uniformly completed by an unblinded statistician who does not participate in the study. Randomization will be performed using a central randomization system (Interactive Web Response Randomization System, IWRS). The subjects, investigators, and all personnel involved in the trial or clinical assessment will remain blinded to the true treatment (except the unblinded drug management team) from the randomization until the database is locked.

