### **SHR8554-201P Study Design and Results**

**(1) Study design:** a multicenter, randomized, double-blind, placebo/active-controlled trial design was used to investigate the efficacy and safety of SHR8554 Injection for postoperative analgesia after elective laparoscopic surgery in the lower abdomen under general anesthesia. A total of 50 subjects with NRS score at rest  $\geq 4$  after elective laparoscopic surgery in the lower abdomen under general anesthesia were planned to be enrolled, including 3 SHR8554 Injection groups, 10 subjects each in each dose group, 10 subjects in the placebo group, and 10 subjects in the active control morphine group. If the subject had at least one score  $\geq 4$  after laparoscopic surgery in the lower abdomen, SHR8554/placebo/morphine will be administered intravenously by an infusion pump at a constant speed over 10 minutes (bolus speed: 30 mL/h) immediately (within 5 minutes after the most recent scoring) for the first time, starting doses: SHR8554 Injection 0.5 mg, 0.75 mg or 1 mg, or morphine 3 mg. Thirty minutes after the first dose, the subjects may self-administer SHR8554 (0.05 mg/dose)/placebo/morphine (1 mg/dose) as needed via Patient Controlled Analgesia (PCA) pump every 10 minutes. PCA administration was stopped 24 h after the starting dose. 3 mL of venous blood was collected before the first dose and at 10 min, 16 h and 24 h after the first dose, respectively, for the analysis of plasma SHR8554 and morphine concentrations.

After administration, the investigator could give antiemetic treatment according to the subject's condition of nausea and vomiting, and tropisetron was preferred for antiemetics (2.5 mg by intravenous injection for the first time, followed by additional doses as needed, and the total dose within 24 h was not more than 10 mg). After administration, for subjects who required rescue analgesia as judged by the investigator due to inadequate analgesia and had NRS score at rest  $\geq 4$ , parecoxib sodium (20 mg by intravenous injection for the first time, followed by additional doses as needed, and the total dose within 24 h was not more than 80 mg) was preferred within 48 h of administration. If the analgesic and antiemetic needs were still not met, the investigator could use other rescue measures as appropriate, and should truthfully record it in the original records and eCRFs.

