### **Data Analysis/Statistical Method**

#### **Sample Size**

With reference to the results of the foreign study TRV130-3002, assuming that the primary efficacy variable SPID24 in the SHR8554 0.75 mg group in this study is comparable to the efficacy in the 0.35 mg group in the TRV130-3002 study, and conservatively assuming that the mean (standard deviation) of SPID24 in the low dose group of this study is 88 (45), and the mean (standard deviation) of SPID24 in the placebo group is 70 (40), it's estimated to need 118 subjects in each group by the sample size calculation formula (PASS) of comparing the means of two samples to achieve the power of 90% with  $\alpha = 0.05$  (two-sided), provided that the four groups are designed in a 1:1:1:1 ratio. Considering the dropout rate of 10%, each group is planned to enroll 132 subjects, with a total of 528 subjects.

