## Statistical Hypotheses and Discriminant Rules

The primary efficacy variable of this trial is SPID24, and the difference test will be used for the group comparison between the experimental group and the placebo group.

Hypothesis:

$$H_0: \mu_T = \mu_C$$

$$H_1: \mu_T \neq \mu_C$$

$\alpha$  level: 0.05 (two-sided).

In this study, the high and low dose groups will be tested sequentially to ensure that the Type I error rate  $\alpha$  is controlled within 0.05 (two-sided). The test between the high dose group and the placebo group will be performed first with  $\alpha$  of 0.05 (two-sided). If there is a significant difference between the high dose group and the placebo group, then the test between the low dose group and the placebo group will be performed with  $\alpha$  of 0.05 (two-sided); if there is no significant difference between the high dose group and the placebo group, only exploratory analysis will be performed for the comparison of the low dose group and the placebo group. For the morphine group, only descriptive statistics will be applied.

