### 7.2.3 Analysis of Subject Characteristics

Age: mean, standard deviation, maximum, minimum and median will be used to describe the age;

Sex: frequency and constituent ratio will be calculated;

Ethnicity: frequency and constituent ratio will be calculated;

Height, weight, and body mass index (BMI): mean, standard deviation, maximum, minimum and median will be used;

CYP2D6, CYP3A4 and CYP3A5 genotypes: frequency and constituent ratio will be calculated according to metabolic phenotype;

ASA classification: frequency and constituent ratio will be calculated;

Past medical history and comorbidities, surgical history, smoking, alcohol consumption and allergy history: frequency and constituent ratio will be calculated;

Surgery: frequency and constituent ratio will be calculated according to the method of anesthesia, and  $\chi^2$  test will be used for comparison between groups; surgery time will be described using mean, standard deviation, maximum, minimum and median;

Whether sufentanil is given intravenously to prevent breakthrough pain: frequency and constituent ratio will be calculated;

Baseline NRS scores: mean, standard deviation, maximum, minimum and median will be used to describe the scores;

Baseline vital signs (blood pressure, respiratory rate, heart rate, body temperature)/oxygen saturation (SpO2): mean, standard deviation, maximum, minimum and median will be used;

Baseline physical examination: frequency and constituent ratio will be calculated for the assessment results of each parameter;

Baseline electrocardiogram: heart rate, PR, QT and QTc intervals will be described using mean, standard deviation, maximum, minimum and median; frequency and constituent ratio will be calculated for ECG assessment results;

Infectious disease screening and drug abuse screening: the frequency and constituent

ratio of the assessment results of each indicator will be calculated.

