### 7.6 Subgroup Analysis

NA

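### Surgical approach (laparotomy or laparoscopy) is not a stated stratification factor, is not listed for tabulation and enters no planned analysis, so the outputs would show neither the mix per arm nor the effect by approach

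*Combined protocol and SAP*

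**What the plan says.** **Eligibility.** Protocol 4.1, criterion 2, admits "Subjects who will undergo selective abdominal surgery (laparotomy or laparoscopy) under general anesthesia". No quota or target share is set for either approach. The objective (Protocol 2.1, SAP 2.1) speaks only of abdominal surgery; the two approaches are named in the description of the population.

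**Allocation.** Protocol 5.2 and SAP 2.5 use the same sentence: "Using a central randomization method, 528 subjects will be randomized in a 1:1:1:1 ratio to 4 treatment groups". Both describe a list generated in SAS and run through an IWRS. Neither names a stratification factor.

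**Description of subjects.** SAP 7.2.3 has a surgery row: "Surgery: frequency and constituent ratio will be calculated according to the method of anesthesia", with a between-group chi-square test and a summary of surgery time. Surgical approach is not in the list.

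**Analysis.** SAP 7.3.1 compares SPID24 by a two-group t-test without covariates. The two sensitivity analyses in SAP 7.5 concern imputation after rescue and the randomized population. The section headed "7.6 Subgroup Analysis" contains only NA, as does SAP 7.7 (Other Analysis).

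**Earlier patient data.** Protocol 1.1 reports one completed patient study, 201P, in "postoperative analgesia after elective laparoscopic surgery in the lower abdomen under general anesthesia".

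**The concern.** Open and laparoscopic surgery can reasonably be expected to differ in the level or time course of postoperative pain, and so in SPID24, although the documents give no figure for this. Open surgery is also new for this drug: 201P was laparoscopic and had about 10 subjects per arm.

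Under the plan as written, the summary tables would look the same whether laparotomy was 5% or 50% of the trial. A reader could not see how many open operations were included, whether the arms were alike in this respect, or whether the effect in open surgery resembled that in laparoscopy. At stake is how far a positive pooled result can be read as covering each approach. A second, smaller matter is that a pre-randomization covariate is left unused.

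**Working it through.** **Inputs from the documents** (Protocol 10.1, 10.3; SAP 2.4): SPID24 mean (SD) 88 (45) in the low dose group and 70 (40) on placebo, so a difference of 18; two-sided alpha 0.05; power 90%; 118 evaluable and 132 enrolled per group.

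**Assumptions** (not in the documents): laparotomy share p from 5% to 50%; difference D in mean SPID24 between approaches from 10 to 30 units; the planning SD includes the variation due to approach; allocation is unstratified.

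**1. The plan's own figure.** Common variance = (45² + 40²)/2 = 1812.5, SD s = 42.57. n = 2(1.960 + 1.282)² × 1812.5/18² gives 118 after rounding up. Then 118/0.9 rounds up to 132, and 4 × 132 = 528. The stated size is reproduced. Power at 118 is 90.1% by the normal approximation and 89.9% by the noncentral t.

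**2. Chance imbalance.** The SD of the difference in laparotomy share between two arms is √(2p(1−p)/132). For p = 0.5 this is 6.2 percentage points, so 95% of imbalances lie within ±1.96 × 6.2, about ±12.1 points. The matching shift in the arm difference is 1.96 × SD × D; with D = 30 it is 3.6 units.

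**3. Gain from adjusting.** Residual variance = 1812.5 − p(1−p)D². For p = 0.5, D = 30: 1812.5 − 225 = 1587.5, SD 39.84. Power = Φ(18/(SD × √(2/118)) − 1.96) = 93.4%.

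**4. Precision by approach.** With m = 118p evaluable per arm, rounded, the 95% CI half-width is 1.96 × s × √(2/m). Power for 18 units within that approach uses the formula in step 3 with s and m. For an 18-unit difference in effect between approaches, the standard error is s × √(2/(118p) + 2/(118(1−p))).

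| Laparotomy share | m per arm | 95% imbalance (points) | Shift for D = 10 to 30 | Adjusted power, D = 10 to 30 | Power within laparotomy | CI half-width | Power, 18-unit interaction |
|---|---|---|---|---|---|---|---|
| 5% | 6 | ±5.3 | 0.5-1.6 | 90.2-90.8% | 11% | 48 | 11% |
| 10% | 12 | ±7.2 | 0.7-2.2 | 90.2-91.4% | 18% | 34 | 16% |
| 20% | 24 | ±9.7 | 1.0-2.9 | 90.4-92.3% | 31% | 24 | 25% |
| 30% | 35 | ±11.1 | 1.1-3.3 | 90.4-92.9% | 42% | 20 | 32% |
| 50% | 59 | ±12.1 | 1.2-3.6 | 90.5-93.4% | 63% | 15 | 37% |

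The table uses normal quantiles, so the half-widths in the smallest groups are somewhat optimistic. By symmetry it also applies to laparoscopy if that is the smaller group.

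**5. Timing.** Protocol section 3 randomizes after surgery, once resting NRS reaches 4. The approach actually performed is therefore known at randomization and cannot be affected by treatment. It is a proper covariate and could serve as a stratum.

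**The case against.** The strongest reply is that nothing here threatens the primary comparison, and that is right. Randomization without stratification is valid, and the pooled test estimates the average effect in the enrolled population with the stated power. Chance imbalance in approach is already covered by the t-test's standard error. Even at the extreme of the assumptions it moves the difference by 3.6 units against a planned 18. The design may also narrow the contrast between approaches, because everyone enters with resting NRS of at least 4 and SPID24 is measured from the subject's own baseline. This does not remove differences in time course, but it makes a gap as large as 30 units less certain.

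Two textual cautions also stand. The randomization specification is not among the documents, so one can say only that no factor is stated; a reader might infer simple randomization, but the text does not say so. And the surgery row in SAP 7.2.3 may be a wording slip for surgical method. If so, it still needs correcting.

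Finally, by-approach estimates cannot establish efficacy in laparotomy. With 10% to 50% of subjects, power for 18 units is only 18% to 63%. This argues for labelling them descriptive. It does not argue for leaving them out: without them, and without a tabulated mix, the reader has no information on open surgery at all.

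**Conclusion.** The point holds as a gap in reporting and a small loss of precision. Approach is not a stated stratification factor, is not listed for tabulation and is not used in any planned analysis, so how well the result applies to each approach could not be judged from the planned outputs.

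A reader might go further and conclude that the trial cannot support its objective, or that laparotomy is half of the indication and goes untested. The documents do not support either. The objective is analgesia after abdominal surgery without reference to approach, the pooled comparison serves it, and no share of laparotomy is stated anywhere.

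The size depends on two unknowns. Adjustment takes power from 90.1% to between 90.2% and 93.4% for shares of 5-50% and differences of 10-30 units. The two parts of the point are not at their worst together: when laparotomy is rare, the precision gain is negligible and the applicability gap is widest; near 50% the reverse holds. The change is worth making because it costs so little.

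**What to change.** Make these changes by dated SAP amendment before unblinding:

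- **SAP 7.3.1:** compare SPID24 by a linear model with treatment and approach, using it for both steps of the high-then-low dose sequence and reporting the adjusted difference with 95% CI. This stays within the analysis-of-variance family named in the protocol. If the t-test is kept as primary, add the adjusted model to SAP 7.5 as a pre-specified sensitivity analysis.
- **SAP 7.6:** replace NA with the SPID24 difference versus placebo and 95% CI by approach, labelled descriptive.
- **SAP 7.2.3:** tabulate approach by arm, and clarify whether the surgery row was meant to do so.
- **Protocol 5.2 / SAP 2.5:** stratify the IWRS list by approach only if the list is not yet fixed. If stratification is already in use, state it.

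Cost: one covariate, one baseline row and one table, with no change in sample size and no added procedures, assuming approach can be taken from the surgical record. The downside is imprecise by-approach estimates, which must not be read as separate tests, and a precision gain that may be close to nil.
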